### Instruments, timing, and modalities of assessment

#### Case 1 (self-assessment)

Pain intensity will be assessed daily using an 11-point (from 0 to 10) visual numeric scale [45]. To help with the assessment, in the paper used for the assessment, the numeric horizontal line will be accompanied with labels and pictures (modified from the Faces Pain Scale [46]) expressing the intensity of pain (Fig. 2). The patient or caregiver will also be asked to report the daily use of on-demand analgesic medications, specifying the type and dosage of drug taken (Fig. 2). The impact of pain on patient daily activities will be evaluated at the baseline and at the end of each week, using a short questionnaire modified from the Back Pain Functional Scale [47]. This is a self-report measure to evaluate the patient’s functional status, proposed for use in both clinical and research settings. It consists of 12 items (derived from existing questionnaires and interviews with physical therapists), investigating work, hobbies, home activities, bending or stooping, dressing shoes or socks, lifting, sleeping, standing, walking, climbing stairs, sitting, and driving. It has been validated [48] and extensively used [49–52], even with older people [53]. The scale was selected among the several available instruments for functional impairment due to chronic pain because of its comprehensiveness combined with a reasonable number of items. The questionnaire takes about 5 min to complete. Although it was conceived as a scale for back pain evaluation, the study authors also judged it as adequate to assess the functional impact of any osteoarticular or neuropathic pain. Although the scale has been used with older people, we slightly modified the Back Pain Functional Scale to make it more appropriate for geriatric patients. We reduced the walking distance from 1 mile (1610 m) to 200 m and the number of stairs from 20 to 10. In addition, we substituted the original rating scale (over six points) with a Likert five-point scale, in which 1 corresponds to ‘no difficulty to perform activity’, 2 to ‘a little bit of difficulty’, 3 to ‘medium difficulty’, 4 to ‘great difficulty’, and 5 to ‘impossibility to perform the activity’. The modified Back Pain Functional Scale is reported in Fig. 3. The total score is obtained as a mean of the scores for all items. When required, the questionnaire will be tailored to the patient usual activity and performance, thus removing those items that do not apply (e.g. if the patient does not drive, the question referring to driving will be removed). If at the enrollment visit the patient appears to value the impairment of one daily activity that is not included in the questionnaire, a specific item will be added.

**Fig. 2 Fig2:**
[figure not shown]
Pain assessment scale

**Fig. 3 Fig3:**
[figure not shown]
Questionnaire for functional status assessment

At the baseline visit, the ability of the patient to compile the questionnaire unaided after instructions will be verified. If any limitation arises, the patient’s caregiver will be engaged and trained to take responsibility for completing the assessment.

#### Case 2 (caregiver-based assessment)

The participating caregiver and treating physician will be asked to identify the pain symptoms and to measure the daily frequency with which the patient complains of them using a five-point scale: 1 corresponds to ‘never’, 2 to ‘once’, 3 to ‘sometimes’, 4 to ‘often’, and 5 to ‘continuously’.

The impact on daily living will be measured by identifying those patient activities most affected by chronic pain (e.g. walking, sleeping, transfers) and building a personalized instrument through which the impact on each activity will be measured using a five-point scale similar to the one used for case 1 patients.

The use of on-demand analgesic medications will be reported daily by the participating caregiver, specifying the type of drug taken and its dosage.

#### Impact of N-of-1 trial on physician’s management plan

To assess the impact of the *N*-of-1 trial on the physician’s management plan, we will preliminarily ask each physician if he or she would treat the patient with um-PEA independently of the *N*-of-1 trial; once the *N*-of-1 trial results become available, we will ask how the physician intends to treat the patient. Management plan options will include continuing or withdrawing um-PEA. We will also investigate the level of the physician’s confidence in the management plan, both before and after the *N*-of-1 trial, using a seven-point scale. The physicians will be asked the following [42]:

How comfortable do you feel now about your treatment plan?Totally comfortable; certain it is the right thing for the patient.Almost totally comfortable; very probably it is the right thing for the patient.Quite comfortable; it is probable that the treatment plan is best for the patient.Not totally comfortable; but treatment likely to be as good as alternatives.Mildly uncomfortable; some uncertainty whether treatment plan is best for the patient.Moderately uncomfortable; feeling that the treatment plan might not be the best for the patient.Extremely uncomfortable; uncertain about treatment plan and, if wrong, patient may suffer.

### Participant timeline

The study timeline is reported in Fig. 1.

At the enrollment visit, eligibility criteria will be checked, informed consent will be obtained, and data regarding patient socio-demographics, pain characteristics, comorbidities, and pharmacotherapy will be collected. The clinical investigators will also evaluate the ability of the patient and the caregiver to assess pain intensity, and appropriate training for questionnaire fulfilment will be performed.

After allocation, the study drug will be delivered to the patient (case 1) or caregiver (case 2) and baseline pain intensity and functional status will be recorded.

The patient or caregiver will be contacted by telephone after the first week of treatment to investigate possible issues concerning therapeutic adherence, adverse effects, and questionnaire completion. A visit with the patient and caregiver will be scheduled before the beginning of each period, to deliver the study drug and acquire the completed questionnaires, checking their correct fulfilment. At the end of the last period, the last questionnaires will be collected.

A final visit with the patient will be scheduled at the end of the trial, once the study results are available. The patient, the caregiver, the treating physician, and the study investigators will discuss the study results.

### Allocation and blinding

The sequence will be generated by the pharmacist using the web site www.randomizer.org. Two sets of two random numbers (numerals 1 [arbitrarily designated as placebo] or 2 [designated as active]), with each number in a set remaining unique, will be generated for each patient. Pharmacists will be recording the allocation sequence and will provide the study drug (either active drug or placebo, indistinguishable) to the clinical investigators at the beginning of each study period. Patients, participating caregivers, treating physicians, and clinical investigators (responsible for outcome assessment and data analysis) will be blinded to the treatment sequence.

Unblinding will be permissible at any time that the trial will be considered concluded. Reasons for which the trial will be deemed concluded other than its completion will be: the patient withdraws consent; the patient or the treating physician is convinced that drug effectiveness has been established or refuted before the end of the designed trial; and safety concerns.

### Sample size

For each *N*-of-1 trial, the sample size is represented by the number of periods of treatment. The choice to design each trial including two treatment pairs is not based on a formal power calculation, considering that *N*-of-1 trials with a practicable number of pairs can rarely reach the conventional level of statistical power of 80–90 % [54]. The choice is a trade-off between the desire of a trial as powerful as possible, and the practical need to limit its duration, given the required length of each period and of the washout between each treatment period. However, considering the actual objective of each *N*-of-1 trial, two treatment pairs seem a reasonable choice, given the starting good level of confidence on the treatment effectiveness that our geriatric team derived from the brief experience with the product (based on conventional trials) we preliminarily had in our practice.

A meta-analysis of the performed *N*-of-1 trials to estimate an overall population treatment effectiveness and evaluate the possible determinants of the effect heterogeneity between trials will be a proof-of-concept study. Given the explorative nature of this secondary objective, the number of *N*-of-1 trials that will be meta-analyzed is not dictated by a specific sample size calculation. A first meta-analysis will be performed on those completed *N*-of-1 trials initiated during the first 12 months from the start of the first *N*-of-1 trial, as long as there are at least three trials. A second meta-analysis will be performed including all the *N*-of-1 trials initiated within 24 months from the start of the first *N*-of-1 trial (study duration).

The posterior probability that um-PEA is better than placebo for a certain patient (single trial) and for the population (trial series) will be provided through a Bayesian approach.

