#### Evaluation of N-of-1 trials on PEA

To evaluate the usage and usefulness of the performed *N*-of-1 trials, each trial will be classified according to:its *completeness*, defining as *complete* those trials conducted to the term; as *incomplete with clinical decision* those trials interrupted before the completion of the planned treatment pairs because the physician and patient or caregiver were at that point convinced of the effectiveness or lack of effectiveness of PEA (notwithstanding the blinding); and as *incomplete for other reasons* those trials interrupted before the completion of the planned treatment pairs because of other reasons (patient compliance, consent withdrawn, concurrent illness, death, etc.);the *achievement of statistically significant results*, setting *P* ≤ 0.1 as the criterion to define a statistically significant mean effect difference between PEA and placebo;the *direction of results*, i.e. a beneficial or harmful effect of PEA compared with placebo when a statistically significant mean effect difference is found.

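### Restricting the first meta-analysis to completed trials leaves out trials stopped on their perceived result, so its pooled effect and heterogeneity can be biased

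*Protocol article*

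**What the plan says.** Four statements in the protocol article bear on the point.

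- **Sample size, first analysis.** "A first meta-analysis will be performed on those completed" N-of-1 trials "initiated during the first 12 months from the start of the first" trial, "as long as there are at least three trials".
- **Sample size, second analysis.** "A second meta-analysis will be performed including all the" trials begun within 24 months. No completion condition is attached.
- **Allocation and blinding.** The list of early endings is introduced by "Reasons for which the trial will be deemed concluded other than its completion will be". Besides withdrawal of consent and safety concerns, it contains the case in which "the patient or the treating physician is convinced that drug effectiveness has been established or refuted before the end of the designed trial".
- **Evaluation of N-of-1 trials on PEA.** Complete trials are "those trials conducted to the term". A separate class, incomplete with clinical decision, holds "those trials interrupted before the completion of the planned treatment pairs because the physician and patient or caregiver were at that point convinced" of effectiveness or its absence.

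The pooled analysis is a secondary, exploratory objective. It is to estimate a population effect and explore what drives heterogeneity between trials. The Meta-analysis section makes the treatment effect fixed in the primary model, with a random patient intercept, and tests a random treatment coefficient second.

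**The concern.** Whether a trial runs to its end depends partly on how its early periods turned out. An analysis limited to trials that ran to the end is then selected on the outcome it is meant to estimate. Stops because a large difference has appeared remove patients with large early differences. Stops because nothing has appeared remove patients with small ones. Either can move the completers' average away from the average over all patients started, and can change the spread of effects that the secondary objective sets out to explain. Safety stops are lost by the same rule.

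The first analysis may rest on as few as three trials, so one exclusion could matter a good deal. The two analyses would also differ in selection rule as well as in window, which clouds any comparison between them.

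**Working it through.** **Step 1: the definitions.** The first meta-analysis takes completed trials. Allocation and blinding sets early stopping on conviction apart from completion. The Evaluation section defines complete as run to the planned end and puts conviction stops in another class. Together these exclude such trials from the first meta-analysis. No section restores them or plans a check on their omission.

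**Step 2: is there a figure to reproduce?** No. The protocol gives no effect size, variance, stopping frequency or sample size for the pooled analysis. Everything below is illustration on assumed values.

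**Step 3: model.** Let a patient's true benefit be θ ~ N(μ, τ²), and let each pair difference be d = θ + error with error SD s. Stopping is judged on d₁ after pair 1. With ρ = τ²/(τ² + s²), E[d₂ | d₁] = μ + ρ(d₁ − μ), so

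completers' mean = μ + ((1 + ρ)/2) × (E[d₁ | continue] − μ).

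**Step 4: signed stopping, μ = τ = s = 1.** SD(d₁) = √2 = 1.414, ρ = 0.5, (1 + ρ)/2 = 0.75.

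- Stop if d₁ > 2.5: z = 1.5/1.414 = 1.061, 14% stop. E[d₁ | continue] = 1 − 1.414 × 0.2273/0.8556 = 0.624. Completers' mean = 1 + 0.75 × (−0.376) = **0.72**.
- Stop if d₁ < 0: z = −0.707, 24% stop. E[d₁ | continue] = 1 + 1.414 × 0.3107/0.7602 = 1.578. Completers' mean = 1 + 0.75 × 0.578 = **1.43**.
- Stop if d₁ < −0.5 or d₁ > 2.5: symmetric about μ, so the mean is 1.00. The variance of true effects among completers is τ²(1 − ρ) + ρ² × Var(d₁ | continue) = 0.5 + 0.25 × 0.644 = 0.661, an SD of **0.81** instead of 1.0.

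**Step 5: blinded stopping on the size of the difference only.** With s = 1.2 and μ = 1 (1,000,000 simulated patients per scenario):

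| Stop after pair 1 if | Stop, τ = 1 | Completers' mean, τ = 1 | Completers' mean, τ = 0 |
|---|---|---|---|
| \|d₁\| > 2 | 29% | 0.60 | 0.80 |
| \|d₁\| > 3 | 10.5% | 0.80 | 0.94 |
| \|d₁\| < 0.5 | 21% | 1.18 | 1.14 |
| < 0.5 or > 3 | 31% | 0.95 | 1.07 |

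With μ = 0 every one of these rules gives a completers' mean of 0.00.

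**Step 6: all started trials, Step 4 cases.** With the between-patient variance in the weights, a two-pair trial has weight 1/(1 + 0.5) = 0.667 and a one-pair trial 1/(1 + 1) = 0.5. In the first case the stopped trials average 1 + 1.414 × 0.2273/0.1444 = 3.226, and the pooled mean is (0.667 × 0.856 × 0.718 + 0.5 × 0.144 × 3.226)/(0.667 × 0.856 + 0.5 × 0.144) = 0.642/0.643 = **1.00**. The second case and all Step 5 scenarios also return 1.00.

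Weighting by number of pairs (2 and 1), which approximates the fixed-treatment-effect primary model, gives (2 × 0.856 × 0.718 + 0.144 × 3.226)/(2 × 0.856 + 0.144) = **0.91** in the first case. In the second the stopped trials average −0.832, and the result is (2 × 0.760 × 1.4335 − 0.240 × 0.832)/(2 × 0.760 + 0.240) = **1.12** (1.13 by simulation). The Step 5 scenarios with τ = 1 give 0.90 to 1.05.

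**The case against.** **Completed may be a timing word.** Each trial lasts 4 × 3 + 3 × 2 = 18 weeks, so trials begun late in the 12-month window would still be running when it closes. The word may only separate finished from ongoing trials. The protocol elsewhere speaks of pooling the trials performed, and the completeness classes are introduced to judge usage and usefulness, not to define an analysis set. This reading is possible. But both sections that discuss early stopping contrast it with completion, and nothing in the text selects the timing meaning. If that is what was meant, the wording still needs to change.

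**The later analysis includes everyone.** This stands. The second meta-analysis is not subject to the exclusion, the pooled objective is exploratory, and individual treatment decisions are untouched. It limits the reach of the point to the first analysis.

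**Stronger readings that the documents do not support.**

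- A reader might infer that the first estimate *is* biased. No stopping frequency is given, opposite stops can cancel, and the cases of zero bias above are real. The signed rules in Step 4 also require the parties to guess the treatment correctly despite blinding.
- A reader might infer that heterogeneity is always understated. With blinded stops on small differences (|d₁| < 0.5, μ = τ = s = 1), the SD of true effects among completers rises slightly, to between 1.02 and 1.03.
- A reader might infer that a change between the two analyses cannot be interpreted at all. They already differ by design in window, and no test of the change is planned. The different selection rule is an avoidable extra difference, no more.

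**Conclusion.** The point holds for the first meta-analysis only. As written, trials stopped on perceived effect or lack of effect, or for safety, are left out. The pooled mean and the between-patient heterogeneity can be biased as a result, in a direction and by an amount that depend on who stops.

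For an assumed true effect of 1.0 point, completers averaged 0.60 to 1.43 across the scenarios. Using all started trials gave 1.00 when between-patient variation in the effect was modelled, and about 0.9 to 1.13 under an approximation to the fixed-treatment-effect model. These figures rest on assumed means, SDs and thresholds, on stopping judged after pair 1 from recorded scores, and on large numbers. They show the mechanism and do not predict this trial's result. With about three trials a random treatment coefficient would be poorly estimated. Safety stops unrelated to the recorded pain scores are not covered by the illustration.

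The change is worth making because the selection is avoidable at almost no cost. It is not a flaw in the trial's primary, individual-patient objective.

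**What to change.** - In Sample size, use one inclusion rule for both meta-analyses: every trial started in the window whose follow-up has ended for any reason, with all available weekly scores.
- In the Meta-analysis section, include the random treatment coefficient, already planned as a second step, when partial trials are pooled. The fixed-effect model alone leaves the smaller residual bias shown above.
- Keep the completed-only analysis as a sensitivity analysis, and report how many trials fall in each completeness class.
- If *completed* was meant only as no longer ongoing, reword the sentence to say that.

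The rule for stopping a trial does not need to change. The cost is a few lines of text, slightly more analysis work, and some trials contributing only partial data. No new data collection is needed, because completed questionnaires are already collected at the visit before each period.

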### Statistical methods

According to the objectives of the study, we will first analyze results within each *N*-of-1 trial and, secondarily, we will combine results across them.

#### Analysis of individual N-of-1 trials

Results on daily pain intensity will be summarized, calculating first the mean symptom score of each week in each period, and then the mean score in each period. The week and period mean scores will be paired with the treatment administered in each period, in a cross-tabulation and in a graph. A similar synthesis will be used for the scores on the week impact on function. A paired *t* test will be used for the statistical comparison of period mean scores within treatment pairs.

At first, the analyses will be performed assuming that the washout periods were sufficient to overcome the possible carryover effect of PEA. If a slow onset time or a residual carryover effect are suspected from the qualitative (‘at a glance’) evaluation of the week (mean) outcome measures including those made during the washout periods, a sensitivity analysis will be conducted. In this second analysis, a paired *t* test will be repeated after having excluded from the calculation of the period mean scores the measures made during the first week of each period.

If more than three measures of the daily pain intensity in the same week are missing for at least one week, the period mean score will be computed, weighting each week mean score according to the inverse-variance method [55].

To make the final treatment decision as objective as possible, the results of each *N*-of-1 trial will first be evaluated by the physician and the patient or caregiver (when feasible), keeping the nature of the two treatments covered (i.e. naming the treatments simply A and B); then, the code will be broken and the nature of treatments revealed.

#### Meta-analysis of N-of-1 trial series

A linear mixed effect model [56] will be performed, with the week mean pain intensity score or the week impact-on-function score as dependent variable and the patient included as random effect (random intercept). The primary analyses will include treatment as the single explanatory variable with fixed effect. Secondly, a random coefficient for treatment (i.e. treatment effect varying between patients) will be tested. A random intercept for pair, in a nested structure (outcome measures within patients, and patients within pairs) will also be tested. A possible residual carryover effect (>2 weeks) will finally be tested, including sequence, pair, treatment by sequence interaction, and treatment by pair interaction as fixed-effects. The models will be also repeated excluding the first week measures of each period.

Patient-level (or study-level) variables will also be tested in the analyses as possible explanatory variables of treatment effect heterogeneity.

In addition to the classic (frequentist) analysis, results of the individual trials and their combination will be approached using Bayesian hierarchical methods, as described by Zucker et al. [57]. Non-informative priors will initially be modeled. In addition, physician’s pre-trial confidence in treatment effectiveness will be used to model informative priors.

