The mechanism of action and the safety profile make PEA an appealing choice for pain relief in older people. However, the evidence base for its efficacy to treat chronic pain in the elderly is not fully convincing. In addition, formulations containing um-PEA, like *Normast®*, are available in Italy only out-of-pocket and a treatment cycle at the doses recommended by the product information sheet would cost the patient about € 60. Given that the required treatment for persistent pain would probably be longer, the cost should be balanced by the actual effectiveness. These reasons represented the rationale to adopt a randomized *N*-of-1 trial as a more objective and personalized prescribing approach, compared with the conventional trial (i.e. ‘prescribe and see’) [39]. In general, *N*-of-1 trials are within-patient randomized multi-period crossover trials to compare, in a double-blind fashion, therapeutic strategies (e.g. an active drug versus no treatments, or two different active therapies), with time periods as randomization units and the patient as control for herself or himself. This study design can be theoretically used to test new drugs along their way to marketing authorization. In our case, we will adopt this approach to determine the best therapeutic choice for a certain patient in clinical practice, objectively and empirically, with randomization and blindness as instruments to overcome those factors (e.g. natural history of the disease, ‘placebo effect’, expectations) that might bias conventional trials of therapies [39–41]. In particular, the series of *N*-of-1 trials on PEA for chronic pain in older patients will be part of the activity of the Geriatric *N*-of-1 Service, an experimental project that we have implemented, with the approval of the local ethical committee, following the pioneering experience of Guyatt and colleagues [42] but in the specific context of geriatric medicine, which suffers most from the limits of parallel group randomized controlled trials, the current paradigms of evidence-based medicine [43].

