### Study objectives

The primary (clinical) objective of our study is to apply the *N*-of-1 trial approach to test the effectiveness of um-PEA 600 mg (*Normast®*) twice a day for chronic pain in a certain patient referring to our geriatric unit in whom the treatment might be indicated, and to assist decisions on long-term treatment of that patient.

As a secondary (research) objective, we aim to obtain an overall estimate of the effectiveness of um-PEA 600 mg twice a day compared with placebo and evaluate the possible determinants of between-trial heterogeneity, through a meta-analysis of the *N*-of-1 trials performed for clinical purposes. Contextually, a classical frequentist meta-analytical approach will be compared with a Bayesian approach, and the potentialities of a Bayesian-based cumulative study design explored.

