### Study design

Each trial will be a blinded placebo-controlled randomized trial. Each trial’s duration will be 18 weeks, comprising two um-PEA and placebo treatment pairs assigned in a random order according to a pairwise randomization scheme. Thus, the sequence of each pair can be either um-PEA/placebo or placebo/um-PEA. Each treatment period will last 3 weeks. The treatment periods of each pair and the two pairs will be separated by 2-week washout intervals to minimize carryover effects. A run-in period will not be routinely performed, but will be considered when deemed appropriate (for example, in case of history of allergies to drugs or drug excipients). Figure 1 summarizes the schedule for the intervention and washout periods.

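### The primary pooled model has no period-level error and no between-patient variation in effect, so its standard error for the average um-PEA effect is generally too small if either source is present

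*Protocol article*

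**What the plan says.** In the protocol article, Statistical methods, Meta-analysis of N-of-1 trial series, the pooled linear mixed model has "the week mean pain intensity score or the week impact-on-function score as dependent variable and the patient included as random effect (random intercept". The fixed part follows: "The primary analyses will include treatment as the single explanatory variable with fixed effect". A random treatment coefficient and a random pair intercept come afterwards as further models to be tested. No rule says that either replaces the primary result.

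The design is stated elsewhere. Background describes N-of-1 trials as designs "with time periods as randomization units and the patient as control for herself or himself". Study design has each trial "comprising two um-PEA and placebo treatment pairs assigned in a random order according to a pairwise randomization scheme" and adds "Each treatment period will last 3 weeks". Washouts lie between all periods: "The treatment periods of each pair and the two pairs will be separated by 2-week washout intervals to minimize carryover effects".

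On the sources of variation, Eligibility criteria admits chronic pain that fluctuates spontaneously, and Study objectives intends to "evaluate the possible determinants of between-trial heterogeneity". Under Sample size, the first meta-analysis goes ahead "as long as there are at least three trials".

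**The concern.** The unit of randomisation is the period, but the unit of analysis is the week. Three weekly means from one period share whatever raised or lowered that patient's pain during those weeks, so they are not three independent looks at treatment. A claim about the average effect across patients must also carry the variation of the effect between patients. The primary model has a term for neither.

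The protocol's own single-trial analysis avoids the first problem: it averages weeks into period means and compares them within pairs. The pooled model drops that step.

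At stake are the confidence interval and P value of the only population-level frequentist estimate that the study yields. The Discussion expects that estimate to inform treatment of patients outside the trials.

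**Working it through.** The protocol states no number of patients, variance component or significance level for the pooled model, so there is no figure of its own to reproduce. The layout checks: 4 × 3 treatment weeks + 3 × 2 washout weeks = 18 weeks, of which 12 are on treatment (6 active, 6 placebo).

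**Assumed inputs** (not in the document): weekly SD σw = 0.8, pair SD σpair = 0.5, two-sided 5%. Period SD σp and between-patient SD of the effect τ are varied, and n is taken from 3 to 20.

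**True variance of the average effect.** Pair effects cancel within pairs. Averaging two periods per arm leaves σp², and averaging six weeks per arm leaves σw²/3:

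V = (τ² + σp² + σw²/3) / n

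**Variance reported by the model** in balanced data: s²/(6n) + s²/(6n) = s²/(3n), with expected

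s² = [n(6σpair² + 9σp² + 11σw² + 3τ²) − 3nV] / (11n − 1)

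**Worked case**, n = 10, τ = 1.0, σp = 0.5:
- V = (1 + 0.25 + 0.213)/10 = 0.146, so the true SE is 0.38.
- s² = [10(1.5 + 2.25 + 7.04 + 3) − 30 × 0.146]/109 = 133.5/109 = 1.225, so the reported SE is √(1.225/30) = 0.20.
- The ratio is 0.53, and type I error ≈ 2[1 − Φ(1.96 × 0.53)] ≈ 30%.

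| σp | τ | true SE (n = 10) | reported SE | ratio | type I error |
|---|---|---|---|---|---|
| 0 | 0 | 0.146 | 0.161 | 1.10 | 3% |
| 0.3 | 0 | 0.174 | 0.168 | 0.97 | 6% |
| 0.5 | 0 | 0.215 | 0.180 | 0.84 | 10% |
| 0.5 | 0.5 | 0.267 | 0.186 | 0.70 | 17% |
| 0.5 | 1.0 | 0.383 | 0.202 | 0.53 | 30% |

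Simulation of 20,000 series per scenario at n = 3, 6, 10 and 20 gives the same percentages to within about one point at every n.

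**When the SE is too small.** For large n, s²/3 = σw²/3 + (2σpair² + 3σp² + τ²)/11. This falls below nV when 5τ² + 4σp² > σpair². With σpair = 0.5 that means σp above 0.25 alone, or τ above about 0.22 alone. Leaving out pair therefore works in the conservative direction, which is why the first row is 3% and not 5%.

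**A second parameterisation**, without pair variance and scaled to the within-patient weekly SD, gives 5% with no extra dependence. Within-period correlation 0.1 gives 8%, 0.2 gives 10–11% and 0.5 gives 19%. An effect SD of 0.25 gives 7%, 0.5 gives 12–13% and 1.0 gives 26–28%. REML fits at n = 10 agree: 5.0%, 10.3% and 18.3% at correlations 0, 0.2 and 0.5.

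**Do the planned later models repair it?** A pair intercept does not: 11–12% at correlation 0.2 and 21–22% at 0.5. For the random treatment coefficient, suppose that a significant 5% F test moves inference to the patient-level contrast (σp = 0.5):

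| n | τ = 1.0: test rejects | τ = 1.0: type I error after switching | τ = 0.5: type I error after switching |
|---|---|---|---|
| 3 | 50% | 17% | 13% |
| 6 | 77% | 9% | 11% |
| 10 | 92% | 6% | 9% |
| 20 | 99% | 5% | 6% |

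**Patient-level contrast on n−1 df:** 5% to within simulation error in every scenario.

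**The case against.** The strongest reply is that pooling is a secondary objective, described as proof of concept, and that the protocol already plans a random treatment coefficient, a pair intercept and a Bayesian hierarchical analysis. The individual treatment decisions use paired comparisons of period means and are untouched. All of this stands, and it limits the severity.

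A reader might infer that the false-positive rate simply is 10–30%. The document does not support that: it gives no variances and no significance level for the pooled model, and weak dependence gives 6–8%.

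A reader might also infer that the later test of the random coefficient would hardly ever reject with few patients. That fails where heterogeneity is large, as the table shows. What remains is that the protocol states no switching rule, and that even with one, error at three patients stays at roughly 10–17% in the heterogeneity scenarios.

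Nor should the missing pair term be counted as a cause of over-optimism, since its omission is conservative.

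Finally, residual covariance and degrees of freedom are details that an article may leave to an analysis plan. The comparison of critical t 2.04 on 11 × 3 − 1 = 32 residual df with 4.30 on 2 df is therefore an assumption about implementation. The fixed and random terms are not: the text sets them.

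**Conclusion.** The point holds conditionally. As written, the primary pooled model omits two variance sources that the protocol itself anticipates, and its standard error is generally too small when either is more than slight relative to the pair variance. Under the assumed SDs, type I error at nominal 5% runs from about 3% (neither source) through 6%, 10% and 17% to about 30% (both strong), and more patients do not cure it. The direction follows from the stated model and design; the size rests on assumed variances. The heterogeneity part concerns the hypothesis of zero average effect across patients. This is a should-fix item in a secondary, exploratory analysis. It does not affect the single-trial paired tests.

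**What to change.** Make the primary pooled estimate a patient-level contrast: for each patient, the mean of the two within-pair differences in period means, tested across patients with t on n−1 df. Where the number of patients supports it, a mixed model with a retained (not merely tested) random treatment effect and period-level error, using small-sample degrees of freedom, would also serve. The two are not equivalent: the simple contrast makes no period adjustment, and a model with fixed period effects and several random terms is too rich for the 12 period means that three patients supply. Use the t reference: with a normal reference the patient-level contrast still has 18–19% error at three patients and about 8% at ten. Keep the random-intercept-only model as a sensitivity analysis.

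The cost is wording only, with no new data. Intervals become wider, and very wide at three patients (critical t 4.30), which is a fair picture of what three patients can say about a population.
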